**Method:**

In a single-blind randomized control trial (RCT), 55 patients with contamination-based OCD will be randomly assigned to four arms. In a factorial design, they will receive 10 sessions of evaluative conditioning training (either sham or real) plus cathodal transcranial direct current stimulation (tDCS) over the orbitofrontal cortex (either sham or real). The intensity of disgust experience and clinical symptoms will be investigated as primary outcomes and quantitative electroencephalogram and cognitive functions as secondary outcomes. The data will be collected at three assessment levels: baseline, after completing intervention sessions, and 2-month follow-up.

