OCD pathophysiology shares neurocircuits and brain structures involved in disgust processing [29]. Among them are the insular cortex and orbitofrontal cortex (OFC). Insular activity is a neural correlate for disgust processing [30, 31]. Insula shows regular higher activity in experiencing actual disgusting stimuli, but the abnormality is when an OCD patient confronts a symptom-provoking stimulus that is not genuinely disgusting. In this situation, insular hyperactivity showed that non-disgusting stimuli are mistakenly perceived as highly disgusting [32]. The insula sends some projections to the OFC [33, 34], the area engaged in coding the aversive value of the stimuli [35], and its enhanced activity, among the insula and other areas, is associated with avoidance behavior in a disgust-relevant situation [36]. The OFC also showed increased gray matter volume in people with higher disgust sensitivity (how much they are distressed when experiencing disgust) [37]. Neuroimaging studies reported the overactivation of OFC in OCD patients [38]. The neuromodulation techniques in this area, such as transcranial direct current stimulation (tDCS), have a therapeutic effect on OCD symptoms [39, 40].

The present study aims to design an EC training targeting disgust toward contamination-related stimuli in C-OCD patients. The hypothesis is that pairing such stimuli with pleasant USs may decline the disgust evoked. The proposed intervention will target lings of disgust more directly and precisely. We will also investigate the effect of brain stimulation over the OFC on disgust processing in C-OCD people. Finally, we are interested in whether adding this neuromodulation technique to the EC training may boost the EC effect. So, we will compare the effectiveness of individual and combined interventions in reducing disgust reactivity.

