## Methods/design

### Study design and setting

This study is a four-arm, randomized, placebo-controlled clinical trial in which participants get sham or real forms of two interventions, including EC and tDCS. It is aimed to investigate the effectiveness of EC, tDCS, and a combination of both on disgust reduction, clinical symptoms, and cognitive characteristics in C-OCD patients. Randomly assignment will be in blocks of 4 in 1:1:1:1 allocation to four parallel groups: (1) real EC plus real tDCS, (2) sham EC plus real tDCS, (3) real EC plus sham tDCS, (4) sham EC plus sham tDCS. We consider sham interventions to be able to separate the exposure effect from the EC effect and also to monitor the placebo effect. Assessments occur at baseline, after completion of 10 interventional sessions, and in a 2-month follow-up. All groups have similar assessments and equal intervention amounts (equal time, activity, and number of sessions). Figure 1 shows the design of the study. The trial will be conducted in the Cognitive Science Laboratory of Ferdowsi University of Mashhad, Mashhad, Iran.

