**Table 1 Tab1:**
[figure not shown]
Procedure schedule

*EC*, evaluative conditioning, *tDCS*, transcranial direct current stimulation, *EEG*, electroencephalography, *DPT*, dot-probe test, *EGNT*, Emotional Go/NoGo test, *ESST*, Emotional Stop-Signal test, *PI-WSUR*, Padua Inventory-Washington State University Revision, *Y-BOCS*, Yale-Brown Obsessive-Compulsive Scale, *DS-R*, Disgust Scale-Revised, *BDI-II*, Beck Depression Inventory-II, *BAI*, Beck Anxiety Inventory, *DRS*, Disgust Rating Scale

The primary outcome measures will be disgust reduction and change in clinical symptoms. We hypothesize that pairing C-OCD-related stimuli with positive USs can reduce disgust feeling toward them in C-OCD patients, and simultaneously cathodal tDCS over left OFC may boost this effect. For that, we will measure the amount of disgust elicited by contaminated stimuli on a Disgust Rating Scale, at baseline and after completing interventions. We will also look for possible transfer effects in OCD symptoms from pre- to post-interventions, measured via PI-WSUR and Y-BOCS. Based on previous studies in which the role of disgust has been implied in the pathology of OCD and the assumption that targeting this negative emotion may have treatment outcomes, it is hypothesized that EC may lead to diminishing C-OCD symptoms, mainly when it is along with cathodal tDCS, over left OFC.

The secondary outcomes include cognitive measures and QEEG recording. Disgust as a negative emotion may affect cognitive functions [61, 62], and OCD patient has been shown to have cognitive deficits in attention, memory, and executive function [63–65]. First, we aim to examine attentional bias and inhibitory control in C-OCD patients when confronted with contaminated stimuli compared with neutral ones. Then, the study will explore whether entering these contaminated stimuli into a positive EC training leads to better performance in these cognitive tests. We are also interested in investigating the correlation of cognitive performance level with the self-reported disgust rating, both at the baseline and after completing interventions. For QEEG recording, we will look for changes in brain wave characteristics from pre- to post-interventions.

We expect a more significant effect for all measures when the EC training is combined with cathodal tDCS than each one alone. We will also detect hypothesized effects at a 2-month follow-up.

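### The protocol asks whether tDCS boosts the EC effect, but the only comparison it states for the combination (combined versus each alone) is met by purely additive effects and cannot show a boost

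*Protocol article*

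**What the plan says.** The question of a boost appears twice. The aims paragraph of the Background says "we are interested in whether adding this neuromodulation technique to the EC training may boost the EC effect". Expected outcomes (text under Table 1) says of the disgust reduction from EC that "simultaneously cathodal tDCS over left OFC may boost this effect".

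Study design and setting fixes what the EC effect is measured against: the sham interventions are there "to separate the exposure effect from the EC effect". The EC effect is therefore real EC minus sham EC.

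For the combination, the Background continues "So, we will compare the effectiveness of individual and combined interventions in reducing disgust reactivity", and Expected outcomes closes with "We expect a more significant effect for all measures when the EC training is combined with cathodal tDCS than each one alone".

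The Abstract calls the design factorial, and Study design and setting describes "1:1:1:1 allocation to four parallel groups" that fill all four cells of a 2 x 2 layout. Statistical analysis names a mixed and repeated-measures MANOVA with group (arm), time and their interactions, at a significance level of 0.05. It names no EC x tDCS term. The last hypotheses paragraph of the Background expects both EC and brain stimulation to lower disgust.

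**The concern.** A boost of the EC effect means that real minus sham EC is larger under real tDCS than under sham tDCS. That is a difference of differences. Showing that the combined arm does better than each single arm answers another question, namely whether giving both is better than giving one.

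The two answers separate in the situation the protocol itself expects, where each component works. A trial with simply additive effects would satisfy the stated comparison, and a report could then say that orbitofrontal stimulation potentiates conditioning when it had only contributed its own effect. The Discussion presents the combination as part of the protocol's novelty, so the distinction matters for the main message. The 2 x 2 design can answer the boost question, but the stated comparison does not use it for that.

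**Working it through.** **1. The plan's own figure.** Sample size gives f = 0.40, 80% power, 95% confidence, three measurements and N = 46. This reproduces as a repeated-measures MANOVA arm x time interaction with 4 arms and 3 times. With s = min(3, 2) = 2, lambda = 46 x 2 x 0.40² = 14.72, df = 6 and 2 x (46 − 4) = 84, and power is 0.8015 (0.790 at N = 45). The powered test is thus an omnibus 6-df test, aimed at neither reading of the combination hypothesis.

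**2. Algebra (no assumed figures).** Let m(EC, tDCS) be the mean reduction in an arm, with 1 = real and 0 = sham:

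- E = m(1,0) − m(0,0), the EC effect under sham tDCS
- T = m(0,1) − m(0,0), the tDCS effect under sham EC
- I = [m(1,1) − m(0,1)] − [m(1,0) − m(0,0)], the boost

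Then:

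- combined minus EC alone: m(1,1) − m(1,0) = T + I
- combined minus tDCS alone: m(1,1) − m(0,1) = E + I

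With I = 0 these equal T and E. Any two positive component effects make the combined arm truly better than each alone with no boost. The comparison is met whenever I > −min(E, T), so it can hold even when tDCS weakens EC.

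**3. Illustration.** The protocol gives no component effects or SD, so the effects below are assumptions. The set-up is one change score with SD 1, pooled-variance t tests, two-sided 0.05 and 11 per arm (55 x 0.80 = 44; 44/4 = 11).

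| True effects (SD units) | Combined numerically best | Significantly beats both single arms | Interaction significant in boost direction |
|---|---|---|---|
| E = T = 0.5, I = 0 | 80% | about 10% | 2.5% |
| E = T = 0.8, I = 0 | about 94% | 29% | 2.5% |
| E = T = 0.8, I = −0.3 | 80% | about 9% | below 1% |

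At N = 46 (12/12/11/11) the figures for significantly beating both, with I = 0, are 10% and 31%. At N = 55 they are 13% and 38%. With 200 per arm they are close to 100%, while the interaction stays at 2.5%. A larger trial therefore does not cure the problem.

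**4. Precision of the right contrast.** At 11 per arm, SE(I) = SD x √(4/11) = 0.603 SD. With t(40) = 2.021, the 95% CI half-width is 2.021 x 0.603 = 1.22 SD. Power for a true interaction of 0.8 SD is about 25%.

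**The case against.** The case on the other side has several parts.

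- **No decision rule is declared.** The sentence in Expected outcomes states an expectation. Nowhere does the protocol say that beating both single arms will be reported as potentiation. This stands. A reader might infer that the trial has committed itself to a false claim, and the text does not support that. The simulated percentages are likewise not false positives for the stated expectation, because in those scenarios the combination really is better than each component. They become errors only if called a boost.
- **Boost may be everyday language** for doing better than EC alone, in which case the wordings agree. That is possible, but it makes a boost indistinguishable from tDCS working by itself, which the Background already hypothesises separately. The sentence in the Background that compares individual and combined interventions may also summarise all three aims and not just the boost question.
- **An analysis plan could name the contrast.** It could, but the protocol's own wording would still offer an easier comparison beside it.
- **More significant effect** could be read as a rule about smaller p-values. The document sets no such rule, and the phrase is most likely loose English for larger.
- **The 0.8 SD scenario** might be taken as the plan's f = 0.40. It is not. The f = 0.40 reproduces N = 46 only for the four-arm by three-time MANOVA interaction, so 0.5 and 0.8 SD are illustrations only.

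**Conclusion.** The point holds as a mismatch between question and comparison. The boost question is an EC x tDCS interaction, while the comparison stated for the combination is met by additive, and even mildly sub-additive, effects. It cannot tell enhancement from addition. This conclusion follows from the algebra and needs only the protocol's hypothesis that both components work.

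The size depends on assumed effects. With 11 per arm and no interaction, both pairwise tests are significant in about 10% (0.5 SD each) to 29% (0.8 SD each) of trials, against about 2.5% for the interaction contrast in the boost direction. These figures assume normal change scores with a common SD at one time point.

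The documents do not show that a boost will be claimed wrongly. They leave that route open, and it is cheap to close.

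**What to change.** In the Background and in Expected outcomes, give each claim its own contrast:

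1. **Boost.** Claim it only from the EC x tDCS (x time) contrast: (real EC + real tDCS minus sham EC + real tDCS) minus (real EC + sham tDCS minus sham EC + sham tDCS), reported with its 95% CI.
2. **Combined better than each alone.** Make this a separate claim that needs both pairwise contrasts to favour the combination, and state that it does not show enhancement of EC.
3. **Wording.** Replace the expectation of a more significant effect with a larger effect, judged on differences between arms.

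The cost is a few sentences and one contrast on data already being collected. The drawback is that a boost becomes harder to claim. At 11 per arm the contrast is imprecise, so it should be read mainly as an estimate, and a non-significant result should not be taken as evidence that tDCS adds nothing to EC.

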### Sample size

We calculated the sample size using the G*Power 3.1 software. To be able to get an effect on our primary outcomes (disgust feeling and clinical symptoms) in three measurements (pre-, post-, and follow-up) at repeated-measure-MANOVA approach, with 95% confidence and 80% power, estimating large effect size with Cohen’s *f* value 0.40, a sample size of 46 participants was calculated. With an attrition rate of 20%, we aim to enroll 55 participants.

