### Statistical analysis

First, data entry will be double-checked. Data quality will be examined regarding data distribution, and outliers will be excluded from further analysis. When these items are ensured, the primary and secondary outcomes will be analyzed in detail using IBM SPSS statistics 25 for Windows (Armonk, NY: IBM Corp). Descriptive statistics (e.g., mean and standard deviation) will be reported for each arm separately. We will conduct the analysis within the intention-to-treat (ITT) framework to investigate the effectiveness of the interventions for all subjects with multiple imputed data sets in case of missing data. The appropriate statistical method will be performed to analyze data. The major one will include mixed and repeated measures of multivariate analysis of variance (MANOVA) to assess the effect of group (arm) and time and their interactions on the result of EEG recordings, computerized tests, and self-report measures as dependent variables. The significant level will be set at 0.05. The covariates, including age, disgust sensitivity, anxiety, and depression, will be considered in the statistical model.

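### The enrolment target of 55 does not match the stated 20% attrition: it leaves 44 completers, two short of the 46 the plan requires (minor)

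*Protocol article*

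**What the plan says.** The Sample size section of the protocol article describes a G*Power 3.1 calculation for the primary outcomes, "in three measurements (pre-, post-, and follow-up) at repeated-measure-MANOVA approach", "with 95% confidence and 80% power", with a large effect of Cohen's f = 0.40. The result and the allowance for loss follow: "a sample size of 46 participants was calculated. With an attrition rate of 20%, we aim to enroll 55 participants". The Method paragraph of the abstract repeats the target: "55 patients with contamination-based OCD will be randomly assigned to four arms". The Statistical analysis section confirms the error rate ("The significant level will be set at 0.05") and plans an intention-to-treat analysis with multiple imputation of missing data. The article does not print the formula that takes 46 to 55.

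**The concern.** An attrition rate is ordinarily the share of enrolled participants who are lost. To end with n participants after losing a share d, one enrols n/(1 − d). Multiplying n by (1 + d) gives a smaller number and always falls short, because the loss applies to the enrolled total and not to the required one. The target of 55 looks like the product of that multiplication.

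At stake is the internal consistency of the sample-size statement. The enrolment target is the figure that an ethics committee, a funder and a reader rely on. As written, the plan says that enrolling 55 absorbs a 20% loss and still leaves the number needed for 80% power, and it does not.

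**Working it through.** **Inputs.** From Sample size: required number 46, attrition 20%, enrolment 55, power 80%, f = 0.40, three measurements. From Statistical analysis: alpha 0.05. From Study design and setting: four groups, allocated 1:1:1:1.

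**Step 1. Reproduce the 46.** The article names the software and a repeated-measures MANOVA but not the option within it. The within-between interaction, with f read as G*Power's f(V), works as follows for k = 4 groups and m = 3 measurements:

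- s = min(k − 1, m − 1) = 2
- df1 = (k − 1)(m − 1) = 6
- df2 = s(N − k − (m − 1) + s) = 2(N − 4)
- noncentrality λ = N·s·f² = N × 2 × 0.16 = 0.32N
- power = probability that a noncentral F(df1, df2, λ) exceeds the 95th percentile of the central F(df1, df2)

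| N | df2 | λ | Power |
|---|---|---|---|
| 46 | 84 | 14.72 | 0.8015 |
| 45 | 82 | 14.40 | 0.7904 |
| 44 | 80 | 14.08 | 0.7787 |

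The smallest N that reaches 0.80 is 46, an exact match. The other options tried (between-factor, within-factor and ANOVA interaction, with two or four groups, two or three measurements, and correlations of 0, 0.3, 0.5 and 0.7) did not return 46.

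**Step 2. Reproduce the 55.**

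- Multiplying: 46 × 1.20 = 55.2, which rounds to 55.
- Dividing: 46/(1 − 0.20) = 57.5, which rounds up to 58.

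Only the first gives 55. Rounding cannot turn 57.5 into 55.

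**Step 3. What 55 delivers.**

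- Expected completers at 20% loss: 55 × 0.80 = 44, which is 46 − 44 = 2 short.
- Largest loss that still leaves 46: 55 − 46 = 9, and 9/55 = 16.4%.
- Check on 58: 58 × 0.80 = 46.4, which meets 46. Check on 57: 57 × 0.80 = 45.6, which does not.

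**Step 4. Size in power.** From the table, complete-case power is 0.7787 at 44 against 0.8015 at 46, a loss of 2.3 percentage points.

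**The case against.** The best case on the other side is that this hardly matters, and much of that case stands.

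- **The shortfall is within the precision of the inputs.** The f of 0.40 is a conventional large effect, not an estimate. On the same model, f = 0.41 gives power of 80.2% at 44. This is a good reason to call the error minor. It does not make the three stated figures agree.
- **Dropouts are not discarded.** The analysis is intention-to-treat with multiple imputation, and a participant lost only at follow-up still contributes earlier data. So 78% is a complete-case figure and not the power of the planned analysis. The planned covariates could also change power. This stands as a limit on the power figure. But imputation does not restore the full information of observed participants, and the plan itself treats attrition as something the required number must be protected against.
- **The power model is inferred.** The article does not name the within-between interaction. The match at 46 is good evidence for it, but the figure at 44 comes from this review. The count of 44 against 46 does not depend on the model.

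Three stronger readings may tempt a reader; the document does not support them.

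- **That the other exclusions have no allowance.** The attrition rate is undefined and may already cover participants removed for new prescriptions or other brain stimulation. The exclusion for invalid baseline responses is listed among criteria for potential participants, and Randomization and blinding places allocation after screening, while Procedure describes assignment before the baseline assessment; the order is unclear. The outlier rule does not say whether values or people are removed.
- **That losses will be well above 20%.** The document gives no such rate.
- **That power must be cut further for several primary scales.** That is a question of multiplicity, separate from attrition, and the plan sets 0.05 with no split of alpha.

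**Conclusion.** The sample-size statement is wrong as written, and the error is minor. A requirement of 46, attrition of 20% and enrolment of 55 cannot all hold: 55 leaves 44, and the matching number is 58. This conclusion rests only on reading attrition as a share of those enrolled. That the authors multiplied by 1.2 is an inference, but the inconsistency does not need it.

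The cost in power is about two points, from 80% to about 78%. That figure assumes the inferred G*Power option, f(V) = 0.40, alpha 0.05 and a complete-case analysis; the planned imputation may recover part of it. A reader might infer that the trial is seriously underpowered because of this slip. The figures do not show that. The abstract carries the same target of 55 and contains no separate error.

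**What to change.** Restate the allowance in the Sample size section, for example: enrolling 55 preserves 46 completers if attrition is at most 16% (9 of 55); at 20% attrition 44 complete, and complete-case power is about 78%. The authors should first confirm which G*Power option they used, since the 78% depends on it, and name it in the same place.

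If the sponsor prefers to keep both 80% power and 20% attrition, the matching enrolment is 58, three more participants than planned, and the abstract must then change as well.

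The restatement costs one sentence, needs no extra participants and changes neither the design nor the analysis. The stated power at 20% attrition becomes slightly less favourable.

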### Randomization and blinding

After screening for inclusion/exclusion criteria and obtaining informed consent, participants will assign to one of four arms through simple randomization with a 1:1:1:1 ratio using a blocked randomization list created by an online program (sealedenvelope.com) in the blocks of 4. The present study protocol is a single-blind design. The participants will be blind that one or both interventions are sham or active until the end of follow-up assessments. The principal investigator will be responsible for enrolment and assigning participants to interventions.

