### Procedure

The enrolled candidate will be invited to an initial interview to confirm eligibility. They also will be provided with detailed information about the trial and procedure and then fill out written consent. Participants who will not meet the eligibility criteria or will not interested anymore will be excluded from the trial. The interview will continue with qualified volunteers in order to record demographic information such as age, gender, education level, age of onset, history of OCD in the family, taking medication or not (if yes, what, since when, and stability duration), and other receiving treatment (past and present) if any.

Participants will be encouraged not to be sleepy or hungry at all sessions in order to be able to focus on tasks appropriately. They will be informed to avoid these conditions in addition to smoking and caffeine consumption from the night before EEG recording.

Once participation is confirmed, an OCD patient will be assigned to one of four trial conditions based on a randomized allocation. A baseline assessment will consist of brain wave recording, computerized cognitive tests, and an online version of self-report measures; it will take about 60 min to complete. After that, as shown in the CONSORT diagram (see Fig. 1), all participants will complete a 10-session intervention. Each session will start with brain stimulation (sham or real); after 5 min, they will be asked to do EC training simultaneously.

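### The principal investigator, not named as blinded, both enrols and assigns from fixed blocks of four with four arms, so many upcoming allocations can be predicted

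*Protocol article*

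**What the plan says.** Under Study design and setting, the protocol article states: "Randomly assignment will be in blocks of 4 in 1:1:1:1 allocation to four parallel groups". Randomization and blinding repeats the block size and describes assignment "through simple randomization with a 1:1:1:1 ratio using a blocked randomization list created by an online program (sealedenvelope.com) in the blocks of 4". Simple and blocked randomization are different methods, so that sentence contradicts itself.

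On blinding, the same section says "The present study protocol is a single-blind design" and then "The participants will be blind that one or both interventions are sham or active until the end of follow-up assessments". No member of staff is named as blind. It closes with "The principal investigator will be responsible for enrolment and assigning participants to interventions".

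On timing, Randomization and blinding places assignment after screening and consent. Procedure reads "Once participation is confirmed, an OCD patient will be assigned to one of four trial conditions based on a randomized allocation" and only then describes the baseline assessment. Participants lists invalid responses on the baseline tests among the exclusions.

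The trial runs at one site and no stratification is mentioned, so there appears to be a single allocation sequence. The planned enrolment under Sample size is 55.

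**The concern.** With four arms at equal allocation and blocks of four, each block is one permutation of the four arms. Whoever knows the first three assignments in a block knows the fourth without seeing the list. The person who makes the assignments knows the past ones, and here that person is also responsible for enrolment.

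The risk is selection bias: whether a candidate is enrolled, or when, could depend on the arm expected next. Criteria such as significant contamination symptoms or a severe comorbidity leave room for judgement, and start dates can be moved. With 55/4 = 13.75, or about 14, participants per arm, a few steered enrolments could matter. Intention-to-treat analysis protects the comparison after randomization but not against selective entry.

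The order given under Procedure adds a second route. If assignment precedes the baseline tests, an exclusion for invalid baseline responses can be made when the arm is already known.

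**Working it through.** The plan states no figure for predictability, so there is none to reproduce.

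**Inputs**
- Four arms at 1:1:1:1, one block size of 4 (Study design and setting; Randomization and blinding).
- 55 participants (Sample size).
- Assumption: the observer knows the block size and all past assignments, has not seen the list, and always guesses the most likely remaining arm.

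**Within one block.** The chance of a correct guess at positions 1 to 4 is 1/4, 1/3, 1/2 and 1. The sum is 25/12 = 2.083 correct guesses per block, and 2.083/4 = 52.1%. Under unblocked simple randomization it is 25% at every position.

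**Over 55 participants.** 55 = 13 × 4 + 3, that is 13 complete blocks and three further positions.
- Expected correct guesses: 13 × 25/12 + 1/4 + 1/3 + 1/2 = 28.17, and 28.17/55 = 51.2%. By chance: 55/4 = 13.75.
- Certain allocations: one per complete block, so 13, and 13/55 = 24%.
- Allocations narrowed to two arms: the third position of the 13 complete blocks and of the incomplete one, so 14.

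**For one factor only** (real or sham evaluative conditioning, or real or sham tDCS). Over the 24 orders of a block, the chance of a correct guess by position is 1/2, 2/3, 2/3 and 1, with mean 70.8% against 50% by chance. The factor level is certain at position 3 in one third of orders and at position 4 always: (0 + 0 + 1/3 + 1)/4 = 1/3 of allocations in complete blocks.

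**What different block sizes would do.** For 55 participants, the fixed-block row is exact. The varying-block rows come from simulation with an observer who knows which sizes are in use, but not their order.

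| Scheme | Correct guesses | Certain allocations |
|---|---|---|
| Fixed blocks of 4 | about 51% | 13 |
| Random blocks of 4 and 8 | about 48% | about 3.8 |
| Random blocks of 4, 8 and 12 | about 45% | about 1.8 |
| Unblocked simple randomization | 25% | 0 |

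If the enroller sees neither the list nor past assignments, guessing falls to 25% whatever the block size.

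**The case against.** The strongest reply is that a journal article commonly leaves list custody and release to the full protocol, so silence on these is not evidence of open allocation. That is right, and it limits the point. A reader might infer that the investigator knows every upcoming allocation. The article does not support this: it names the online program as the source of the list and does not say who holds it. Predictability does not need that fact. It follows from the stated block size, the number of arms and one person holding both roles.

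A reader might also infer that the investigator judges eligibility. This is not stated. Recruitment has a therapist check the full criteria for candidates who come through flyers or advertisements, and Procedure names no interviewer. What is stated is responsibility for enrolment, which still leaves its decision and timing open to influence.

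It would likewise be too strong to say that no analysis can help. Statistical analysis plans adjustment for age, disgust sensitivity, anxiety and depression, and models the outcomes over time. This can reduce measured imbalance, but unmeasured selection remains.

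Two practical objections stand in part. First, varying blocks of 4 and 8 alone lower correct guesses only from about 51% to 48%, so they cannot be the main remedy. Second, the timetable leaves little room. Trial status expects the last follow-up by the end of September 2023. Taking off the 2-month follow-up and about two weeks for ten sessions at five a week puts the last enrolment near mid-July 2023, about four weeks after the registration date of 16 June 2023 that the article reports.

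Finally, 'simple' reads as a slip, since both sections specify blocks of 4. It needs correcting but adds no weight.

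**Conclusion.** The point holds as a weakness in what the article states, not merely as missing detail. One person, not named as blinded, is responsible for enrolment and assignment, under a fixed and published block size equal to the number of arms. For an observer who knows past assignments, about 51% of the 55 allocations can be guessed correctly against 25% by chance, and 13 are certain. The order of assignment and baseline under Procedure aggravates this, because one exclusion depends on baseline tests. That reading rests on the text alone, since the flow chart and schedule table are not available here.

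The figures assume that past assignments are known to whoever enrols, which follows if the investigator makes them. All 55 would be known in advance only if the investigator also held the list, which the article does not say. Nothing shows that steering has occurred. The finding is that the design permits it and that the planned adjustment could correct only part of it. This should be changed where participants remain and disclosed where they do not.

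**What to change.** **For remaining participants**
- Have someone who does not enrol hold the list, for example an existing trial steering committee member, or use a web release system.
- Release each assignment only after eligibility, consent and the baseline assessment are complete and recorded. Reconcile the order under Procedure with the baseline-test exclusion under Participants.
- As far as possible, keep past assignments from the person who enrols; otherwise prediction from the block pattern remains.
- As a supplement, use undisclosed, randomly varying block sizes of 4 and 8.
- Delete 'simple' under Randomization and blinding.

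**For participants already allocated**
- Report who held the list, how each assignment was concealed and released, and whether any exclusion followed assignment. State the predictability as a limitation.

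**Cost.** A regenerated list for those still to enter and a short amendment. No new body is needed, because the steering committee exists. Arm sizes may differ by one or two at the end. If no one remains to be enrolled, only the text correction and the disclosure apply.
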